**Abstract**

Recommended standards of care do not, ironically, include the prescription of exercise to target and ameliorate the progressive health decline and overall feeling of well-being in patients with atrial fibrillation. Recent Standards for the Provision of Cardiac Rehabilitation of Ontario are calling for the consideration for referral and enrollment of patients with atrial fibrillation in cardiovascular rehabilitation – evidence is needed to support and confirm these efforts. The main purpose of this project is to evaluate the effects of high-intensity interval training (HIIT) compared to moderate-intensity continuous exercise training (MICE) on exercise capacity and quality of life in patients with persistent or permanent atrial fibrillation. Positive results from this study will identify a new intervention that: produces important improvements in patient-rated clinical, behavioural and exercise outcomes; provides mechanistic insight into the role of exercise training in the management of atrial fibrillation; requires minimal equipment; and is appealing to patients with atrial fibrillation.

**Background**

Atrial fibrillation is the most common sustained cardiac arrhythmia, with a lifetime risk of 26% in persons aged 40 years and older. Given an aging population, burgeoning rates of obesity and diabetes, and the growing number of patients who have experienced various forms of heart disease and their complications, the prevalence of atrial fibrillation is expected to increase. The presence of atrial fibrillation substantially increases the risk of stroke, and significantly reduces exercise tolerance (-20%). In fact, declining exercise capacity is often the presenting symptom leading to the diagnosis of this arrhythmia. Mechanisms of exercise intolerance in persons with atrial fibrillation are not well defined but presumed to be due to poor heart rate control, loss of atrioventricular synchrony and declining cardiac output. Excessive heart rate responses to exercise may have deleterious effects on ventricular function further limiting exercise capacity. Persons with atrial fibrillation, because of disordered cardiac function and diminished exercise tolerance, typically report poor quality of life. The restoration of sinus rhythm or the slowing of the rate of atrial fibrillation has been shown to improve symptoms and quality of life. However, adequate heart rate control at rest does not imply adequate control during exercise. Despite the presence of exercise intolerance, poor quality of life, weight gain and an associated decline in overall health among patients with atrial fibrillation, recommended standards of care do not, ironically, include the prescription of exercise to target and ameliorate these significant health issues.

Exercise training is a recognized form of treatment of persons with heart disease. A few studies have demonstrated the beneficial effects of moderate-intensity continuous exercise training in patients with atrial fibrillation. Although demonstrating positive results, these studies have significant limitations including small sample size, lack of follow-up measures, poor study design and high withdrawal rates. A novel exercise paradigm such as high-intensity interval training, a form of exercise in which

participants alternate periods of short, intense, non-oxidative exercise with less intense recovery periods, may be more efficient and motivating, and may help to improve adherence to exercise training in atrial fibrillation patients. A training program that offers a smaller time commitment is advantageous as “lack of time” remains a commonly cited barrier to routine exercise participation even among cardiovascular disease patients. Given the growing number of trials in cardiovascular disease patients demonstrating the safety and superiority of high-intensity interval training compared to moderate-intensity continuous exercise training, investigations determining the type of exercise training intervention most effective in improving clinical, exercise and behavioural outcomes in those with atrial fibrillation are needed. It is likely that high-intensity interval training (compared to moderate-intensity continuous exercise training) will attenuate the rate of heart rate acceleration to a greater degree enabling persons with atrial fibrillation to be more active. Such outcomes would lead to significant improvements in exercise capacity and quality of life. To date, no studies have evaluated the potential benefits of high-intensity interval training in those with atrial fibrillation. The Ontario Standards for the Provision of Cardiac Rehabilitation are calling for such research.

### **Purpose/Objective and Rationale**

The primary objective of this study is to evaluate, in adults with persistent or permanent atrial fibrillation from baseline to 12 weeks follow-up, the effects of moderate-intensity continuous exercise training and high-intensity interval training on exercise capacity and quality of life. Secondary objectives include evaluating the effects of moderate-intensity continuous exercise training and high-intensity interval training on: exercise adherence; activity status; atrial fibrillation-specific quality of life; symptom burden; self-reported symptom frequency and severity; anxiety and depressive symptoms; insomnia severity; sleep apnea risk; and, self reported sleep patterns; heart rate (HR) control; lower body muscular fitness; and exercise capacity measured by cardiopulmonary exercise test (CPET) [in a subset of willing participants].

### **Hypotheses**

In adults with persistent or permanent atrial fibrillation, a 12-week program of high-intensity interval training will be superior to moderate-intensity continuous exercise training in improving: 1) exercise capacity measured by 6-minute walk test distance; and, 2) quality of life measured by the physical component summary (PCS) measure of the Short Form 36 Health Survey Questionnaire (SF-36). Further, a 12 week program of high-intensity interval training will be superior to moderate-intensity continuous exercise training in improving: 1) exercise adherence measured by accelerometer (and verified by the 7-day FITT log; 2) activity status measured by the Duke Activity Status Index (DASI); 3 ) atrial fibrillation specific quality of life measured by the University of Toronto Atrial Fibrillation Severity Scale (AFSS); 4) symptom burden measured by the Canadian Cardiovascular Society Severity of Atrial Fibrillation (CCS-SAF) scale; 5) self-reported symptom frequency and severity measured by the 7-day symptom diary; 6) anxiety and depressive symptoms measured by the Hospital Anxiety and Depression Scale (HADS); 7) insomnia severity measured by the Insomnia Severity Index; 8) sleep apnea risk measured by the STOP-BANG Sleep Apnea Questionnaire; 9) self reported sleep patterns measured by the 7-day sleep diary; and, 10) HR control measured by 24-hour Holter ECG recordings and ECG recordings at each CPET; 11) lower body muscular fitness measured by standard load tests; and 12) exercise capacity measured by cardiopulmonary exercise test (CPET) [in a subset of willing participants].

## **Clinical Relevance**

Positive results from this study will identify a new intervention that: produces important improvements in patient-related clinical, behavioural and exercise outcomes; provides mechanistic insight into the role of exercise training in the management of atrial fibrillation; requires minimal equipment; and is appealing to patients with atrial fibrillation.

## **Design**

This is a single-centre, randomized controlled trial to evaluate the effects of high-intensity interval training when compared to moderate-intensity continuous exercise training on exercise capacity and quality of life in patients with persistent or permanent atrial fibrillation.

## **Setting**

This trial will be conducted at the University of Ottawa Heart Institute (UOHI). Specifically, all testing and exercise training will be performed in the Cardiac Diagnostic Centre, on Track in the Division of Prevention and Rehabilitation, or the *Goodlife* exercise facilities at The Ottawa Hospital – Civic Campus.

## **Inclusion and Exclusion Criteria:**

Inclusion criteria:

1. persistent or permanent atrial fibrillation;
2. rate controlled with a resting ventricular rate of equal to or less than 110 bpm;
3. able to perform a symptom-limited exercise test;
4. at least 40 years of age;
5. patient agrees to sign informed consent.

Exclusion criteria

1. currently participating in routine exercise training (more than two times per week);
2. unstable angina;
3. uncontrolled diabetes mellitus;
4. diagnosed severe mitral or aortic stenosis;
5. diagnosed hypertrophic obstructive cardiomyopathy with significant obstruction;
6. unable to provide written, informed consent.

## **Sample Size**

The sample is sufficient to test the two primary research hypotheses simultaneously using repeated measures mixed models analyses (group: (1) moderate-intensity continuous exercise training, (2) high-intensity interval training; time: (1) baseline, (2) 12 weeks follow-up). A sample size of 48 participants (24 per group) is needed to detect a difference of 67 m on the 6-minute walk test (6MWT) between the two groups at a two-sided 0.025 significance level with 80% power, assuming that the standard deviation (SD) of the response variable is 150 m. The minimal clinically important difference (MCID) for the 6MWT is estimated to be 54-80 m using both distributional and discriminative methods. A sample size of 98 participants (49 per group) is needed to detect a difference of 5 points in the physical component score (PCS) between the 2 groups on the Short Form-36 questionnaire (SF-36) with a two-sided 5% significance level and 80% power, assuming the SD of the response variable is 10 points.

The MCID in quality of life as measured by the PCS of the SF-36 is a change score of 5. We will use the larger sample of the two as the study size to ensure we have adequate power for both hypothesis tests. We will use an ‘intention to treat’ strategy in our primary analysis, however we adjusted our sample size upward to account for a planned 10% loss to follow-up to allow a secondary analysis using only participants with complete outcome data. We therefore plan to randomize 108 participants in the trial.

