### **Intervention**

Following the baseline phase, participants will be randomized in a 1:1 ratio to: 1) standard care + moderate-intensity continuous exercise training (to be completed in the University of Ottawa Heart Institute cardiovascular rehabilitation setting), or 2) standard care + high-intensity interval training using a blocked, stratified, random sequence that is computer-generated. Treatment assignments will be generated and placed in sealed, numbered envelopes to ensure concealment until baseline data are collected.

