**Primary Outcome & Primary Measures (endpoints):**

There will be two primary outcomes: 1) changes in quality of life measured by the Short Form 36 Health Survey Questionnaire (SF-36); and, 2) changes in exercise capacity measured by the 6 minute walk test (6MWT) over the 12 week intervention period.

Quality of life: will be measured using the widely used and thoroughly validated SF-36 questionnaire. It yields an 8-scale profile of functional health and well-being scores as well as psychometrically-based physical and mental health summary measures.

Exercise capacity: will be measured using the 6MWT. Patients will be instructed to walk as far as possible for 6 minutes. The 6MWT is highly reproducible, and 6MWT distance performance is highly correlated with objective measures including VO2peak and survival.

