### **Analyses of Results**

Repeated measures mixed models analyses will be performed to examine changes in primary and secondary outcomes.

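### The primary mixed model states no common baseline mean or baseline covariate; in its ordinary form it is a change-score comparison that gives up precision

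*Protocol*

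**What the plan says.** The model appears in the Sample Size section: a repeated measures mixed model with factors "group: (1) moderate-intensity continuous exercise training, (2) high-intensity interval training; time: (1) baseline, (2) 12 weeks follow-up". Baseline is thus one of the two levels of time, that is, part of the response.

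The Analyses of Results section is a single sentence: "Repeated measures mixed models analyses will be performed to examine changes in primary and secondary outcomes". The section on the primary outcome also speaks of change over the 12 weeks, for example "changes in quality of life measured by the Short Form 36 Health Survey Questionnaire (SF-36").

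Under Intervention, allocation follows the baseline phase, is 1:1 and is made "using a blocked, stratified, random sequence that is computer-generated". Assignments stay concealed until baseline data are in. The stratification factors are not named.

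The protocol does not say which contrast is tested, whether the baseline means are held equal, or whether any covariate enters the model. It gives no baseline to week-12 correlation, and it does not say whether its SDs refer to one visit or to change.

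**The concern.** A mixed model with group, time and their interaction, and with baseline as a free response, estimates a separate baseline mean in each arm. Randomisation comes after baseline, so the true baseline means are the same in both arms. Estimating them separately discards that knowledge. With two visits, the interaction test then reduces to comparing mean changes, which subtracts the whole of the baseline value however weakly it predicts the week-12 value. ANCOVA, or a mixed model with one common baseline mean, uses baseline only as far as it predicts.

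What is at stake is precision, not bias. The protocol claims adequate power for both primary hypotheses. Baseline is already measured for both outcomes, so the loss is avoidable.

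**Working it through.** **Inputs from the Sample Size section.** PCS: difference 5 points, SD 10, two-sided 5%, 80% power, 49 per group. 6MWT: "A sample size of 48 participants (24 per group) is needed to detect a difference of 67 m on the 6-minute walk test", "at a two-sided 0.025 significance level with 80% power", "assuming that the standard deviation (SD) of the response variable is 150 m". The trial uses the larger size. It randomises 108 with 10% loss planned, and 108 × 0.9 = 97.2, so about 49 per group complete. Rho is not given and is assumed over 0.3 to 0.9.

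**The plan's own figures.** With n per group = 2[SD(z₁₋α/₂ + z₀.₈₀)/Δ]²:
- PCS: 2[10(1.960 + 0.842)/5]² = 62.8, so 63 per group, against 49 stated.
- 6MWT: 2[150(2.241 + 0.842)/67]² = 95.3, so 96 per group, against 24 stated.

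Neither stated size follows from its own two-sided inputs. That is a separate defect. It matters here because it leaves no spare precision to give away.

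**Variances.** Let σ be the single-visit SD and n the number per group.
- Difference in mean change: (2σ²/n) × 2(1 − rho).
- Baseline-adjusted: (2σ²/n) × (1 − rho²).
- Ratio, adjusted to change: (1 + rho)/2, below 1 for every rho below 1. It is 0.65, 0.75, 0.85 and 0.95 at rho 0.3, 0.5, 0.7 and 0.9.

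**Check by simulation.** In 100 simulated trials (49 per group, rho 0.6), the unconstrained group-by-time estimate agreed with the difference in mean change to within 1e-13. Its empirical SD was 1.77, against 1.56 for both the constrained-baseline model and ANCOVA. The model-based variance ratio was 0.80, as (1 + 0.6)/2 predicts.

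**Power at 49 per group** (noncentral t, 96 df, noncentrality Δ/(SD_eff √(2/49))). PCS is tested at two-sided 0.05 and 6MWT at two-sided 0.025.

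Reading A: the stated SD is a single-visit SD, so SD_eff is SD√(2(1 − rho)) for change and SD√(1 − rho²) when adjusted.

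| rho | PCS, change → adjusted | 6MWT, change → adjusted |
|---|---|---|
| 0.5 | 69% → 81% | 48% → 61% |
| 0.6 | 78% → 87% | 58% → 69% |
| 0.7 | 89% → 93% | 72% → 79% |

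Example, PCS at rho 0.5: SD_eff is 10√1 = 10 for change and 10√0.75 = 8.66 adjusted. The noncentrality is 2.475 and 2.858.

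Reading B: the stated SD is the SD of change, so SD_eff is SD for change and SD√((1 + rho)/2) when adjusted.

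| rho | PCS, change → adjusted | 6MWT, change → adjusted |
|---|---|---|
| 0.5 | 69% → 81% | 48% → 61% |
| 0.7 | 69% → 76% | 48% → 55% |

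The two readings coincide at rho 0.5 because 2(1 − 0.5) = 1.

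**The case against.** The strongest reply is that the protocol lists factor levels and leaves the contrast, the constraints and the covariates to an analysis plan that is not shown. A constrained-baseline mixed model also has group, time and baseline as a response, so the proposed remedy fits the stated text. With randomisation, the unconstrained test is unbiased and holds its type I error, so the choice could be called a preference.

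Much of this stands, and it limits what may be inferred:
- **That the plan is certainly a change-score analysis.** The text does not exclude a common baseline mean. The point holds for the ordinary unconstrained form, which is the natural reading of group and time factors aimed at change.
- **That the plan ignores the randomisation strata.** This would rest on silence. Moreover, a stratum effect that is constant over time cancels in a change contrast: in 500 simulated trials of 98 patients with a strong constant effect, the mean standard error was 1.425 without the stratum term and 1.424 with it. Since the factors are unnamed, no gain from them can be quantified.
- **That adjustment restores 80% power.** On reading A this needs rho of about 0.5 for PCS and about 0.7 for 6MWT. On that reading the plain change score already reaches 80% for PCS at rho of about 0.62. On reading B, 6MWT is still at 61% after adjustment at rho 0.5.
- **That one linear model suits every secondary outcome.** The 0 to 4 symptom-severity scale and the symptom-diary frequencies are not obvious candidates.

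The reply does not remove the core. The protocol describes a specific model and targets change, and a more precise method using data already collected is available on either reading of the SD.

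**Conclusion.** The point holds as a matter of efficiency. In its ordinary unconstrained form, the stated model yields a variance 2/(1 + rho) times that of a baseline-adjusted analysis: 1.54 times at rho 0.3, 1.33 at 0.5, 1.18 at 0.7 and 1.05 at 0.9. The gain in power at 49 per group is 12 percentage points for PCS and 13 for 6MWT at rho 0.5. At rho 0.7 it is 4 to 7 points for each outcome, depending on the meaning of the SD.

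This rests on equal variances at the two visits, complete pairs of visits and an assumed rho. The direction does not depend on rho; the size does. The analysis should be changed, but the results would not be invalid if it were not.

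**What to change.** State in the protocol or analysis plan that the primary analysis of 6MWT and PCS estimates the high-intensity minus moderate-intensity difference at 12 weeks. Use a mixed model with the baseline mean constrained equal across arms, or ANCOVA with baseline as covariate. The constrained model also retains participants seen only at baseline, which suits the planned intention-to-treat analysis.

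Name the factors used in the stratified randomisation and include them as fixed effects, without claiming a particular gain. Use the same approach for continuous secondary outcomes that have a baseline value, and choose a suitable model for ordinal and count outcomes. State the assumed rho and whether each SD refers to a single visit or to change.

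The cost is wording only. The sample-size calculation must be corrected separately.

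### The 6MWT sample size does not follow from its stated inputs: they need about 96–97 per group, not 24, so the claim of adequate power for both primary tests is unsupported as written

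*Protocol*

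**What the plan says.** The Sample Size section of the protocol gives a complete calculation for the walk test: "A sample size of 48 participants (24 per group) is needed to detect a difference of 67 m on the 6-minute walk test (6MWT"), "at a two-sided 0.025 significance level with 80% power", "assuming that the standard deviation (SD) of the response variable is 150 m". It quotes an MCID of 54–80 m. A separate calculation for the SF-36 physical component score gives 98 participants (49 per group). The section then sets the trial size: "We will use the larger sample of the two as the study size to ensure we have adequate power for both hypothesis tests". The SF-36 figure is treated as the larger and raised for 10% loss to 108 randomised.

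Three other statements bear on the calculation:
- The same section says that the two primary hypotheses will be tested "using repeated measures mixed models analyses", with measurements at baseline and 12 weeks.
- The primary outcomes section defines the walk-test outcome as "changes in exercise capacity measured by the 6 minute walk test (6MWT) over the 12 week intervention period".
- Under Intervention, "participants will be randomized in a 1:1 ratio".

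The protocol states no correlation between baseline and week 12, and no second SD for the walk test.

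**The concern.** A difference of 67 m against an SD of 150 m is a standardised effect of 67/150 = 0.45. Twenty-four per group is far too few to detect that with 80% power at a two-sided 0.025 level. The SF-36 calculation assumes a slightly larger standardised effect (5/10 = 0.50) and a less strict significance level, yet asks for twice as many participants. The two results cannot both be right under one method.

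The walk test is one of two primary outcomes, and the rule for choosing the trial size depends on which calculation gives the larger number. If the walk-test figure is wrong, the wrong outcome may have set the size, and the assurance of adequate power for both tests has no basis.

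**Working it through.** **Inputs (Sample Size section unless noted).** Difference 67 m; SD 150 m; two-sided alpha 0.025, so z = 2.2414; power 80%, so z = 0.8416; allocation 1:1 (Intervention section).

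**Required size.** n per group = 2(2.2414 + 0.8416)² × (150/67)² = 2 × 9.505 × 5.012 = 95.3, so 96. By the noncentral t distribution, power is 79.7% at 96 and 80.2% at 97, so 97. The total is 192–194. The stated 24 per group (48) is a quarter of this.

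**Other test conventions, SD 150 m (normal / t, per group).**
- Two-sided 0.05: 79 / 80
- One-sided 0.05: 62 / 63
- One-sided 0.10: 46 / 46

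None gives 24.

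**Routes that do give the stated figure.**
- A smaller SD. Solving for 24 per group gives 75.3 m (normal) or 73.2 m (t), about half the stated SD.
- A within-person correlation r, with 150 m as the SD of a single measurement. For a change score the requirement is 95.3 × 2(1 − r); setting this to 24 gives r = 0.874. With baseline adjustment it is 95.3 × (1 − r²); setting this to 24 gives r = 0.865.
- A one-sample formula, (150 × 3.083/67)² = 47.6, rounded to 48 and then split into two groups. This uses the stated SD and would simply be the wrong formula for a two-group comparison.

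The documents do not say which of these, if any, was used.

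**Power at the planned size, taking 150 m as the SD of the analysed response (noncentral t, two-sided 0.025).**

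| Per group | Power for 67 m | Difference detectable with 80% power |
|---|---|---|
| 24 (as stated) | 23% | 137 m |
| 49 (evaluable) | 48% | 95 m |
| 54 (all randomised) | 52% | 90 m |

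The normal approximation gives 24%, 49% and 53%, and 133, 93 and 89 m. At 49 or 54 per group the detectable difference lies above the whole quoted MCID range of 54–80 m.

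**Sensitivity if 150 m is a single-measurement SD.** The correlations below are assumptions, because the protocol gives none. Power is for 67 m at 49 per group, noncentral t.

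| r | Change score | Baseline-adjusted |
|---|---|---|
| 0.50 | 48% | 61% |
| 0.70 | 72% | 79% |
| 0.75 | 80% | 85% |
| 0.80 | 89% | 92% |
| 0.87 | 98% | 99% |

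**Does one correlation explain both calculations?** The SF-36 inputs (5 points, SD 10, two-sided 5%, 80% power) give 62.8 per group without any adjustment. Reaching the stated 49 with a change score needs 62.8 × 2(1 − r) = 49, so r = 0.61. With baseline adjustment, 62.8 × (1 − r²) = 49, so r = 0.47. Neither is close to 0.87, so a common repeated-measures adjustment does not account for the pair.

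**The case against.** The strongest defence is that the analysis is a repeated measures model using baseline and week 12, and that 150 m is the spread of a single walk distance. Correlation between the two walks would then reduce the variance of the comparison. At r of about 0.75 a change-score analysis with 49 per group already reaches 80% power, and at the r of about 0.87 that reproduces 24 per group it is about 98%. If 150 m is a slip for 75 m, the trial is likewise well powered and only the text is wrong.

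This stands as a limit on the conclusion. A reader might infer that the trial simply has about 48% power for the walk test. The documents do not support that without a condition: the figure holds only if 150 m is the SD of the quantity compared between groups. Nor is 48% the only figure on that reading. Intention to treat is the primary strategy, and 54 per group gives 52% if every randomised participant contributes to the analysis.

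The defence does not rescue the calculation as printed. The protocol calls 150 m the SD of the response variable and defines the outcome as a change, so read plainly 150 m is the SD of what is analysed. The correlation needed is high and not stated.

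Two further inferences should be resisted. The rule of taking the larger sample is sound; it is the walk-test figure fed into it that fails. And the protocol does not say how a null result would be interpreted, so no misreading can be attributed to it.

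**Conclusion.** The point holds as an inconsistency between stated inputs and stated result. The inputs need about 96–97 per group (192–194 in total) against the 24 per group (48) given, a factor of four that neither rounding nor the choice of test explains. On those inputs the walk test, not the SF-36, would have set the trial size, and the claim of adequate power for both hypothesis tests is not supported.

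The mismatch rests only on the protocol's own figures and a standard two-group comparison. The power of about 48–52%, and the detectable difference of about 90–95 m, rest on one further assumption: that 150 m is the SD of the analysed response, as worded. If it is a single-measurement SD, true power depends on an unstated correlation and could exceed 80%. The correction is needed in either case, because this calculation supports the power claim for a primary outcome.

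**What to change.** Establish which SD was meant, then take one of two routes in the Sample Size section.

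(a) If 150 m is the SD of the analysed response: replace 48 (24 per group) with 192–194 (96–97 per group). State that 108 randomised gives about 48% power for 67 m with 49 evaluable per group and 52% with all 54 analysed, with 80% power for about 95 m and 90 m respectively. Delete the claim of adequate power for both tests.

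(b) If a smaller SD, an SD of change or a baseline-adjusted residual SD was intended: state that SD, or the correlation, with its source, and recompute both the sample size and the power at the planned size with a two-group formula.

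Recheck the SF-36 figure in the same edit. Its stated inputs give 63 per group (64 by the t-test), and 49 per group gives about 69% power (t-test) unless some unstated adjustment applies.

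The cost is protocol wording; neither route requires more enrolment. Under (a) the stated power becomes less favourable; under (b) the SD or correlation has to be justified.

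### The two primary hypotheses are sized at inconsistent significance levels (0.025 for 6MWT, 0.05 for SF-36 PCS), and no rule is stated that links them

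*Protocol*

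**What the plan says.** The Sample Size section of the protocol opens by stating: "The sample is sufficient to test the two primary research hypotheses simultaneously using repeated measures mixed models analyses". It then makes two calculations.

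- 6MWT: a difference of 67 m, "assuming that the standard deviation (SD) of the response variable is 150 m", compared "between the two groups at a two-sided 0.025 significance level with 80% power". The result given is 24 per group.
- SF-36 PCS: a difference of 5 points, "with a two-sided 5% significance level and 80% power, assuming the SD of the response variable is 10 points". The result given is 49 per group.

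The larger of the two sets the study size, so the PCS calculation at 5% drives the 108 to be randomized.

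The Hypotheses section lists the two outcomes as separate superiority hypotheses, the second being "quality of life measured by the physical component summary (PCS) measure of the Short Form 36 Health Survey Questionnaire (SF-36"). The primary outcome section is looser: "There will be two primary outcomes: 1) changes in quality of life measured by the Short Form 36 Health Survey Questionnaire (SF-36"). It then describes the instrument's eight scales and its physical and mental summaries without saying which score is primary. The Analyses of Results section names only the repeated measures mixed model. It gives no significance level and no success rule.

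**The concern.** Halving alpha for one of two primary outcomes makes sense when each outcome can support a claim on its own and the 5% is shared between them. Giving the other outcome the full 5% in the same paragraph, for tests said to be made together, undoes that split. A reader cannot tell whether success on either outcome is enough, whether both are needed, or whether one test opens the way to the other.

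Two things depend on the answer. One is the chance of a false primary claim. The other is the PCS power: its calculation sets the trial's size, and it uses a level that is not available unconditionally if 6MWT also takes a share of 5%.

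The loose naming of the SF-36 endpoint adds a smaller ambiguity about which score the PCS calculation is meant to serve.

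**Working it through.** **Inputs, all from the Sample Size section.** 6MWT: difference 67 m, SD 150 m, two-sided 0.025. PCS: difference 5 points, SD 10 points, two-sided 0.05. Power 80% for each; 24 and 49 per group stated. The protocol gives no correlation between the two outcomes, so the values below are assumptions.

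**Step 1. The plan's own figures.** For two groups, n per group = 2 × [SD × (z for alpha + z for power) / difference]².

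- 6MWT: 2 × [150 × (2.241 + 0.842) / 67]² = 95.3, so 96 per group against 24 stated.
- PCS: 2 × [10 × (1.960 + 0.842) / 5]² = 62.8, so 63 per group against 49 stated.

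Neither stated size follows from its stated inputs. That is a separate matter. It is noted here because the power figures below start from under 80% for this reason, before any change of alpha.

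**Step 2. Family-wise error if either outcome can support a claim, both null hypotheses true.**

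- Upper bound: 0.025 + 0.05 = 0.075.
- Independent outcomes: 1 − (1 − 0.025)(1 − 0.05) = 0.0738.
- Correlated outcomes: 1 − P(|Z1| < 2.241 and |Z2| < 1.960) under a bivariate normal distribution.

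| Assumed correlation | Family-wise error |
|---|---|
| 0 | 7.4% |
| 0.3 | 7.2% |
| 0.5 | 6.9% |
| 0.7 | 6.5% |

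**Step 3. Family-wise error if both must succeed.** A false claim requires rejecting at least one true null hypothesis while the other test also rejects. The error therefore cannot exceed the larger single level, 0.05. Each outcome could then be tested at 0.05, and 0.025 for 6MWT buys nothing.

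**Step 4. A stepwise rule.** Holm compares the smaller p-value with 0.025 and, if that is significant, the other with 0.05. A fallback rule tests 6MWT at 0.025, then PCS at 0.05 if 6MWT is significant and at 0.025 if it is not. Both hold the family-wise error at 5% and both use 0.025 and 0.05. Under either, PCS reaches 0.05 only after 6MWT has succeeded.

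**Step 5. Power at 49 per group on the stated inputs (two-sample t-test).**

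- PCS at 0.05: 68.8%. PCS at a fixed 0.025: 58.0%.
- 6MWT at a fixed 0.025: 47.6%.
- PCS under Holm, independent outcomes: 0.580 + (0.688 − 0.580) × 0.476 = 0.631, about 63%.

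The first term is PCS passing at 0.025 by itself. The second is PCS falling between 0.025 and 0.05 while 6MWT has passed at 0.025.

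**The case against.** The strongest reply is that the two levels appear only in the sample size calculations. The analysis section sets no level, and a statistical analysis plan that is not shown may state the decision rule. This limits the point: the protocol does not show that the tests will be run at 0.025 and 0.05, and the absence of a multiplicity method is not the complaint. It does not remove it. The protocol already fixes two levels that do not fit together for tests made simultaneously, and the one at 0.05 determines the trial's size.

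Three stronger readings are tempting and are not supported.

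- A reader might infer that the trial's family-wise error is 7.5%. That figure is an upper bound and needs a rule that either outcome suffices, which the protocol does not state. The wording of the hypotheses and the aim of adequate power for both tests do not settle the matter either way.
- A reader might infer that no sound rule can combine 0.025 with 0.05. Holm and the fallback rule both do. The protocol describes neither: it gives PCS 0.05 without condition, and simultaneous testing speaks against a sequence.
- A reader might infer that the primary outcome section makes all the SF-36 scores primary. It names the instrument and describes what it yields. The hypothesis and the sample size both specify the PCS. The wording should be aligned, but no extra endpoints are declared.

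**Conclusion.** The inconsistency is real and stands in the protocol's own text: two simultaneous primary tests sized at unequal levels, with no order, both-must-succeed requirement or overall alpha to explain them.

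Its size is conditional. With each outcome tested at its stated level and either able to support a claim, the excess over 5% is at most 2.5 percentage points, and about 2 points at assumed correlations of 0.3 to 0.5 (7.2% and 6.9%). With both required, there is no excess.

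The consequence for power is that the stated 80% for PCS cannot be carried over to a rule that holds 5% overall. On the stated inputs it is about 58% at a fixed 0.025 and about 63% under Holm. The Holm figure assumes independent outcomes.

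This should be fixed. It can be cured by wording and its effect on error depends on an unstated rule, so it does not by itself invalidate the primary claim.

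**What to change.** State one decision rule that holds the overall two-sided alpha at 0.05, before any outcome data are seen by group. A suitable choice is Holm across 6MWT distance and SF-36 PCS: the smaller p-value against 0.025, then, if significant, the other against 0.05, with success on either outcome. If the intention is that both must succeed, say so and use 0.05 for each.

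In the Sample Size section, use levels that follow from the chosen rule and restate the power of both outcomes under it at the planned size, without enrolling more.

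In the primary outcome section, name the SF-36 PCS as the primary score and treat the other SF-36 scores as secondary, in line with the Hypotheses and Sample Size sections.

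The cost is wording, plus one disadvantage to accept openly: under Holm, PCS faces a stricter first-step threshold and the protocol must report a lower power for it than the 80% now claimed.
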